### Strategies to improve adherence to interventions {11c}

No specific strategies to improve adherence to interventions are foreseen.

### Relevant concomitant care permitted or prohibited during the trial {11d}

No concomitant care will be prohibited during the trial.

### Provisions for post-trial care {30}

A no-fault insurance is foreseen for all trial participants.

### Outcomes {12}

Primary end-point
To show that FFS after vsAR is non-inferior to tAR after 24 months of follow-up.❖ Failure is defined as the inability to pass a 16-Fr flexible cystoscope through the reconstructed area without damaging the urethral mucosa. This anatomical definition of failure was chosen based on the fact that it has—to the best of our knowledge—the highest sensitivity and specificity to detect stricture recurrence after urethroplasty. In our opinion, this end-point leaves little to no room for interpretation, whereas a functional definition of failure (“need for re-intervention”) might be strongly influenced by the treating physician (e.g., physicians who personally favor technique A over B might be more reluctant to offer redo surgery to this group compared to patients treated with technique B, thus introducing the biased result that A would be better than B because fewer patients have to be re-operated during the follow-up period).❖ The non-inferiority limit, *d*, was set at 10%. This non-inferiority limit was chosen based on experts’ opinion, 5 patients’ opinion and a round-the-table consensus discussion.❖ The fact that failure after AR usually occurs within the first years after surgery serves as the rationale behind the follow-up interval of 24 months in this study [13].

Secondary end-points
To analyze change in erectile function and differences in change of erectile function between vsAR and tAR.❖ The International Index of Erectile Function (IIEF-5) questionnaire* will be administered to participants preoperatively and after 3, 12, and 24 months of follow-up.❖ The IIEF-5 questionnaire provides a summative score between 5 and 25 and should be interpreted as follows: 22–25 = no erectile dysfunction; 17–21 = mild erectile dysfunction; 12–16 = mild to moderate erectile dysfunction; 8–11 = moderate erectile dysfunction; 5–7 = severe erectile dysfunction.❖ De novo postoperative worsening of erectile function will be defined as a decrease of ≥ 5 points on the postoperative IIEF-5 questionnaire compared to the preoperative IIEF-5 questionnaire. This definition was chosen based on experts’ opinion, taking into account the lack of studies describing the ideal cut-off value to delineate “de novo erectile dysfunction” for this 5-item questionnaire [12].To analyze change in ejaculatory function and differences in change of ejaculatory function between vsAR and tAR.❖ The Male Sexual Health Questionnaire—Ejaculatory Dysfunction short form (MSHQ-EjD short form) questionnaire** will be administered to participants preoperatively and after 3, 12, and 24 months of follow-up.❖ The MSHQ-EjD short form questionnaire, consisting of 4 questions, provides a summative score between 1 and 15 (question 1–3) and a bother/satisfaction score between 0 and 5 (question 4).To analyze change in lower urinary tract symptoms (LUTS) and differences in change of LUTS between vsAR and tAR.❖ The International Consultation on Incontinence Questionnaire—Male Lower Urinary Tract Symptoms module (ICIQ-MLUTS module) questionnaire** will be administered to participants preoperatively and after 3, 12, and 24 months of follow-up.❖ The ICIQ-MLUTS module, consisting of 7 questions, provides a summative score between 0 (asymptomatic) and 24 (most symptomatic) (question 1–6) and a bother score between 0 (not bothersome) and 3 (very bothersome) (question 7).❖ Remark: The 7 questions of the ICIQ-MLUTS module questionnaire are only a subset of the entire ICIQ-MLUTS questionnaire. These 7 questions were chosen because of their relevance in a setting of urethral stricture disease and were validated in English, Dutch, and other languages (cfr. infra).❖ Peeling’s voiding picture** will be administered to participants preoperatively and after 3, 12, and 24 months of follow-up.❖ Peeling’s voiding picture provides a score between 1 and 4.To analyze change in urinary incontinence and differences in change of urinary incontinence between vsAR and tAR.❖ The International Consultation on Incontinence Questionnaire—Urinary Incontinence short form (ICIQ-UI short form) questionnaire will be administered to participants preoperatively and after 3, 12, and 24 months of follow-up.❖ The ICIQ-UI short form questionnaire, consisting of 3 scoring questions and 1 self-diagnostic question, provides a summative score between 0 (asymptomatic) and 21 (most symptomatic).To analyze change in quality of life and differences in change of quality of life between vsAR and tAR.❖ The EQ-5D-3L questionnaire** will be administered to participants preoperatively and after 3, 12, and 24 months of follow-up.❖ The EQ-5D-3L module, consisting of 5 questions, provides a 5-digit score in which every digit varies between 1, 2, and 3.❖ The EQ—Visual Analogue Scale (EQ-VAS)** will be administered to participants preoperatively and after 3, 12, and 24 months of follow-up.❖ The EQ-VAS provides a scale between 0 and 100.To analyze patient satisfaction and differences in patients’ satisfaction between vsAR and tAR.❖ Two specific questions regarding patient satisfaction will be asked at 3, 12, and 24 months.To analyze change in maximum flow rate (Qmax) and differences in Qmax between vsAR and tAR.❖ Uroflowmetry will be performed preoperatively and after 3, 12 and 24 months of follow-up.To analyze postoperative (< 90 days) complication rate and differences in postoperative (< 90 days) complication rate between vsAR and tAR.❖ Complications within the first 90 postoperative days will be categorized according to the Clavien-Dindo classification system [15, 16].

* The IIEF-5 questionnaire is a validated tool to assess erectile function and can be used in patients undergoing urethroplasty [17, 18].

** These subsets of questions were validated in English and in Dutch in a setting of patients with urethral strictures undergoing urethroplasty [19, 20].

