### Eligibility criteria {10}

Inclusion criteria for participants:
Voluntarily signed written informed consent according to the rules of ICH-GCP (Declaration of Helsinki) and national regulations.Age ≥ 18 years.Male patient.Fit for operation, based on the surgeon’s expert opinion.Isolated short (≤ 3 cm) bulbar urethral stricture confirmed by imaging. Imaging includes at least retrograde urethrography (RUG). In case of equivocal findings, voiding cysto-urethrography (VCUG) and urethroscopy must be added.Patient is able and willing to comply with the postoperative protocol.

Exclusion criteria for participants:
Absence of signed written informed consent.Age < 18 years.Female patients.Transgender patients.Patients unfit for operation.Concomitant urethral strictures at other urethral locations (penile urethra, membranous urethra, prostatic urethra, bladder neck).Urethral strictures > 3 cm.Urethral stricture(s) at other urethral locations (penile urethra, membranous urethra, prostatic urethra, bladder neck).Lichen sclerosus-related strictures.Strictures after failed hypospadias repair.Patients with neurogenic bladder.Shift of technique to augmented urethroplasty or any technique other than AR due to any circumstance. These patients will be logged, but will be excluded (post-hoc) from further analysis within this trial.History of pelvic radiation therapy.Active treatment to enhance erectile function (such as PDE5-inhibitors and intracavernous injections) at the moment of prescreening for inclusion in this trial.Any condition or situation, which, in the investigator’s opinion, puts the patient at significant risk, could confound the study results, or may interfere significantly with the patient’s participation in the study.Patient declares that it will be impossible for him to attend the follow-up consultations.

Eligibility criteria for participating centers:

Only urethral surgeons who state that they are sufficiently capable of performing both vsAR and tAR are allowed to participate in this trial.

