## Statistical methods

### Statistical methods for primary and secondary outcomes {20a}

ITT analyses will be used for all end-points.

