### Interim analyses {21b}

A formal interim analysis for safety is planned when the 3-month follow-up data of the first 50 randomized patients are obtained. This analysis will be performed by the independent third party for safety and the trial coordinator. The following stop criteria have been predefined:
3 m-FFS of vsAR and its two-sided 95% CI are entirely beneath the 3 m-FFS of tAR – 10%.> 30% difference between vsAR and tAR in de novo postoperative worsening of erectile function, defined as a decrease of ≥ 5 points on the postoperative IIEF-5 questionnaire compared to the preoperative IIEF-5 questionnaire.

If one of the stop criteria is reached, the independent third party for safety will discuss this with the central PI and the central Ethical Committee, and a decision about prematurely stopping the trial will be formulated and communicated to all parties involved in the trial.

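### Men with a baseline IIEF-5 of 5 to 9 cannot have the erectile-worsening event but stay in its denominator, which dilutes the risk difference and the >30% interim criterion

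*Protocol article*

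**What the plan says.** **Definition.** Under Outcomes {12}: "De novo postoperative worsening of erectile function will be defined as a decrease of" at least 5 points on the IIEF-5 relative to the preoperative score. The same section states: "The IIEF-5 questionnaire provides a summative score between 5 and 25". Its lowest bands are "8–11 = moderate erectile dysfunction; 5–7 = severe erectile dysfunction".

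**Who is analysed.** Statistical methods {20a} states: "ITT analyses will be used for all end-points". No minimum baseline score is set for this end-point. Eligibility criteria {10} exclude "Active treatment to enhance erectile function (such as PDE5-inhibitors and intracavernous injections) at the moment of prescreening", but do not exclude untreated erectile dysfunction.

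**Treatment after surgery.** Section {11d} states: "No concomitant care will be prohibited during the trial". For secondary end-points, the analysis section censors participants only when they have a further urethral treatment. Starting erectile treatment is neither an event nor a reason for censoring.

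**Where the definition is used.** It serves the two-sided Fisher's exact tests at 3, 12 and 24 months (20% level), the per-protocol analysis in {20b}, and one of the two interim stop criteria in {21b}: a more than 30% "difference between vsAR and tAR in de novo postoperative worsening of erectile function", assessed on the 3-month data of the first 50 randomised patients.

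**The concern.** A man who cannot register the event is not at risk of it. Keeping him in the denominator pulls both arms' risks towards zero and narrows the absolute difference between them. A fixed absolute threshold such as 30% then depends on how many men with low scores happen to be recruited, which has nothing to do with the two operations.

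The second issue is comparability over time. Men on erectile treatment are kept out at entry, so baseline scores are untreated by design, whereas follow-up scores may be treated. A man who loses function, is treated and returns to within 4 points of his baseline counts as not worsened.

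At stake is the size of the reported difference in erectile worsening, the first functional benefit that the introduction suggests for vessel sparing, and the meaning of the only functional stop criterion.

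**Working it through.** **Inputs from the protocol.** Scale minimum 5; event is a fall of at least 5; stop threshold 30%; interim on 50 patients, so about 25 per arm; 50 per arm with 20% drop-out, so 50 × 0.8 = 40 per arm at the end; two-sided Fisher's exact test at 0.20.

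**The plan's own figure.** No rate, power or sample size is stated for erectile worsening, so there is nothing to reproduce for this end-point. The primary sample size does reproduce: 95.4% v 95.3%, margin 10%, one-sided alpha 0.10 and power 0.80 give 40.8, so 41 per arm as stated. It is not affected.

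**Assumptions (not in the protocol).** s = share with baseline below 10, taken as equal in both arms, 10% to 30%. m = share of worsened men whose score is restored by treatment. The event rates among men who can worsen are illustrative.

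**Step 1, the floor.** The lowest possible follow-up score is 5, so the baseline must be at least 5 + 5 = 10. From 9, a fall of 5 would give 4, which is off the scale. Scores 5 to 9 cover all of the severe band and half of the moderate band (8 and 9 out of 8 to 11).

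**Step 2, dilution.** Observed difference = true difference among men who can worsen × (1 − s). True difference needed to reach the threshold = 30 / (1 − s):

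- s = 10%: 30 / 0.9 = 33.3 points
- s = 20%: 30 / 0.8 = 37.5 points
- s = 30%: 30 / 0.7 = 42.9 points

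**Step 3, chance of crossing the interim criterion.** Exact binomial, assumed rates of 45% v 10% among men who can worsen, 25 per arm: 0.67 with s = 0, then 0.55, 0.43 and 0.30 for s = 10%, 20% and 30%. Restricting to baseline of at least 10 at s = 20% leaves 20 per arm and gives 0.58 instead of 0.43. It does not return to 0.67, because the set is smaller and the smallest crossing difference rises from 8/25 = 32% to 7/20 = 35%.

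**Step 4, the final Fisher test.** Exact power, 40 per arm before restriction:

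| Assumed rates in men who can worsen | s | All 40 per arm | Baseline ≥ 10 only (n per arm) |
|---|---|---|---|
| 30% v 10% | 10% | 0.73 | 0.73 (36) |
| 30% v 10% | 20% | 0.67 | 0.68 (32) |
| 30% v 10% | 30% | 0.60 | 0.62 (28) |
| 20% v 5% | 10% | 0.62 | 0.66 (36) |
| 20% v 5% | 20% | 0.55 | 0.61 (32) |
| 20% v 5% | 30% | 0.48 | 0.54 (28) |

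With s = 0 the powers are 0.78 and 0.69. At 30% v 10% and s = 20%, the estimated difference is 20 × 0.8 = 16 points in all men and 20 points in the at-risk set. The restriction therefore corrects the estimate but recovers little power.

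**Step 5, masking.** With treatment restoring some scores, the factor becomes (1 − s)(1 − m). As an illustration, s = 20% and m = 25% give 0.8 × 0.75 = 0.6. The threshold then needs 30 / 0.6 = 50 points, the chance of crossing in Step 3 falls to 0.18, and a 20-point difference shows as 12. Nothing in the protocol supports a particular m.

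**The case against.** **Floor patients hardly harm the planned test.** They are non-events in both randomised arms, so the null hypothesis remains valid, and risk among all randomised men is a legitimate ITT quantity. This stands: Step 4 shows a gain of 0.02 or less at 30% v 10%, and 0.04 to 0.07 at 20% v 5%. A reader might infer that the erectile comparison is lost. The protocol does not support that, because it also compares the full IIEF-5 change by Mann-Whitney test at each visit, and that comparison registers smaller falls, including from low baselines.

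**The 30% threshold may have been meant for all randomised men.** Nothing says that it was set for men with baseline of at least 10. Crossing it leads to a discussion with the central PI and the Ethical Committee rather than an automatic stop, and an independent third party assesses harm every two months. A reader might infer that safety oversight is disabled; it is not. What remains is that the meaning of a fixed absolute threshold shifts with case mix.

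**Sizes are assumed.** This stands. If few men start below 10, the effect is small, and excluding men already on erectile treatment may lower that share. Masking also needs treatment to bring the score back to within 4 points of baseline.

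**Treatment start should not be part of the main event.** A reader might infer that it should. The protocol's own reasoning points the other way: for the primary end-point it rejects need for re-intervention because the physician influences it, and outcome assessors are not blinded. A man with untreated dysfunction at entry could also be counted as newly worsened without any fall in score. Scoring regardless of treatment is a recognised approach, although the protocol does not state that it was chosen.

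**Part of this may sit elsewhere.** The list of collected variables is not shown, so treatment start may already be recorded, and an analysis plan may add sensitivity analyses. The definition itself, without an at-risk set, is fixed in the protocol.

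**Conclusion.** The point holds for the estimate and the interim criterion. Men with baseline 5 to 9 are guaranteed non-events, and the absolute difference shrinks by (1 − s): the 30% criterion needs 33 to 43 points among men who can worsen if 10% to 30% of men start below 10. That range is an assumption.

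The mismatch between untreated baseline and possibly treated follow-up scores is also real and can mask some worsening, but its size cannot be derived from the protocol.

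The point does not extend to a serious loss of Fisher power from keeping floor patients, nor to the primary end-point, its sample size, or the Mann-Whitney comparison of IIEF-5 change.

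**What to change.** 1. For de novo erectile worsening, at interim, final and per-protocol analysis, define the at-risk set as patients with baseline IIEF-5 of at least 10. Report the number below 10 in each arm, and give the all-randomised result alongside. State which set the >30% criterion refers to; the proposal is the at-risk set, with the threshold itself unchanged.
2. Record at each follow-up visit whether erectile treatment has been started, if the data collection does not already do so.
3. Keep the score-only definition as the main one, and add a sensitivity analysis that counts treatment start as worsening.

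The cost is one case report form item, a few sentences of analysis wording and a smaller denominator (32 instead of 40 per arm at s = 20%), so the at-risk estimate is less precise and the interim comparison noisier. Treatment status that is not recorded at the visits may not be recoverable later. No change to patient care is involved.

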#### Analysis of the secondary end-points

Postoperative changes in erectile function, ejaculatory function, LUTS, urinary incontinence, and quality of life will be analyzed by comparing the scores of the postoperative questionnaires with the scores of the preoperative questionnaires. For every participant, the 3-, 12-, and 24-month follow-up questionnaire scores will be compared to the respective preoperative questionnaire scores. Differences in scores will be logged for the 3-, 12-, and 24-month follow-up moment, and for each of these time-points, the median (interquartile range (IQR)) change in scores will be assessed for vsAR and tAR. Median (IQR) change in scores will be compared between vsAR and tAR using a two-sided Mann-Whitney *U* test at the 20% significance level.

As regards de novo postoperative worsening of erectile function, defined as a decrease of ≥ 5 points on the postoperative IIEF-5 questionnaire compared to the preoperative IIEF-5 questionnaire, a two-sided Fisher’s exact test at the 20% significance level will be used to compare vsAR and tAR at the 3-, 12-, and 24-month follow-up moment.

Postoperative patient satisfaction will be assessed at the 3-, 12-, and 24-month follow-up moment. For each time-point, the proportion of satisfied patients will be compared between vsAR and tAR using a two-sided Fisher’s exact test at the 20% significance level.

Postoperative change in Qmax will be compared between vsAR and tAR at the 3-, 12-, and 24-month follow-up moment using a two-sided Mann-Whitney *U* test at the 20% significance level.

Postoperative complications will be compared between vsAR and tAR using a two-sided Fisher-Freeman-Halton test at the 20% significance level.

Note that for all secondary end-points, participants will be censored at the moment they undergo a subsequent urethral treatment (dilation, urethrotomy, urethroplasty, or urinary diversion).

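### The EQ-5D-3L outcome is defined only as a five-digit code, but the analysis subtracts and ranks it as a score, so the result depends on the order of the digits

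*Protocol article*

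**What the plan says.** One secondary objective in Outcomes {12} is "To analyze change in quality of life and differences in change of quality of life between vsAR and tAR". Two measures serve it, both collected before surgery and at 3, 12 and 24 months. The EQ-5D-3L "provides a 5-digit score in which every digit varies between 1, 2, and 3". For the other measure, "The EQ-VAS provides a scale between 0 and 100". The section on plans for assessment and collection of outcomes {18a} again lists both as the measures of change in quality of life.

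The section on analysis of the secondary end-points sets one rule for the questionnaires and includes quality of life by name: "quality of life will be analyzed by comparing the scores of the postoperative questionnaires with the scores of the preoperative questionnaires". The rule has three steps:

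- Each man's baseline value is subtracted from his value at each of the three visits.
- These changes are then summarised by arm: "the median (interquartile range (IQR)) change in scores will be assessed for vsAR and tAR".
- The arms are tested against each other on these changes by a Mann-Whitney U test, two-sided, with significance taken at 20%.

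No exception is made for the EQ-5D-3L. No index, value set, level sum or per-dimension outcome is mentioned anywhere. Other multi-item instruments are given a total to which the rule can be applied. For example, "The IIEF-5 questionnaire provides a summative score between 5 and 25".

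**The concern.** A code such as 11121 records the answers to five separate questions. It looks like a number, but the place value of each digit has no clinical meaning. The rule for the secondary end-points needs a quantity for which a difference has a direction and differences can be put in order. The only EQ-5D-3L outcome that the protocol defines does not have that property.

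If the rule is followed literally, the dimension written first dominates and the one written last counts for almost nothing. The median change, its sign and the ordering of patients in the Mann-Whitney test would all depend on the layout of the questionnaire. Functional benefit, including quality of life, is part of what the trial sets out to examine, and three planned comparisons (3, 12 and 24 months) are affected.

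**Working it through.** The plan gives no figure to reproduce here. The check applies the stated analysis to the stated outcome.

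**Inputs.** Five digits, each 1, 2 or 3 (Outcomes {12}), give 3^5 = 243 possible codes and 243 × 242 / 2 = 29,403 pairs of different codes. A higher digit is taken as a worse level. The operations are post minus pre, median, and Mann-Whitney U (analysis of the secondary end-points).

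**Step 1: weights implied by subtraction.** For digits d1 to d5,

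code = 10000·d1 + 1000·d2 + 100·d3 + 10·d4 + d5.

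A one-level worsening therefore scores 21111 − 11111 = +10000 in the first dimension and 11112 − 11111 = +1 in the last.

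**Step 2: one dimension better by a level and another worse by a level.**

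- In the first two digits: 12111 − 21111 = −9000.
- In the last two digits: 11112 − 11121 = −9.

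Both read as improvements, only because the improving dimension is written before the worsening one.

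**Step 3: the sign can contradict most of the answers.** From 12333 to 21111, one dimension is one level worse, one is one level better and three are two levels better. The sum of levels falls from 12 to 6, a change of −6. The code changes by 21111 − 12333 = +8778, a worsening.

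**Step 4: how widespread this is among the possible states.** Counting over all 29,403 pairs:

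| Property of the pair | Pairs | Share |
|---|---|---|
| Each state better than the other on at least one dimension, so code order is arbitrary | 21,870 | 74.4% |
| Ranking flips if the five digits are written in reverse order | 14,094 | 47.9% |
| Code order opposes level-sum order | 5,960 | 20.3% |
| Level sums equal but codes differ | 4,355 | 14.8% |

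The level sum is only a yardstick for direction, not a proposed score. The counts treat all states equally and do not predict how often the problem arises in trial patients.

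**Step 5: does ranking rescue it?** Take an invented example with 40 men per arm (the planned 50 less 20% drop-out). In each arm 20 men improve by one level and 20 do not change.

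- *Improvement in the first digit in arm A and the last digit in arm B.* The changes are −10000 or 0 in A, and −1 or 0 in B. Counting the pairs in which A exceeds B, with ties as one half: U = 20 × 20 + 0.5 × 20 × 20 = 600, out of 40 × 40 = 1,600. The two-sided p-value is 0.037, below the protocol's 0.20.
- *Improvement in the same digit in both arms.* U = 800, p = 1.0.
- *The first case with the digits written in reverse order.* U = 1,600 − 600 = 1,000. By symmetry the p-value is again 0.037, now in favour of the other arm.

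Ranking removes the size of the place values but keeps the order that they impose.

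**The case against.** **The protocol never says that the five digits are read as one integer.** This is true. The sentence may only describe what the questionnaire yields, and the authors do not call this score summative as they do others. A comparison digit by digit, or of a derived index, could be what they have in mind. A reader might infer that the sponsor intends to subtract codes, and the text does not establish that. But neither alternative appears in the document, and the code is the only EQ-5D-3L quantity offered to a rule that demands differences.

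**Scoring detail belongs in the analysis plan.** A value set could well be named in a document not shown. Mere silence on scoring would not be a finding. Here, however, the article fixes both the form of the outcome and the analysis applied to it, and the two do not fit together.

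**Quality of life is still covered.** This stands. A reader might conclude that the whole quality-of-life objective fails. It does not: the EQ-VAS runs from 0 to 100, is collected at the same visits and suits the stated test.

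**The test is rank-based and the arms are randomised.** This also stands. The gap between −9000 and −9 does not enter a rank test as a distance. The code is a fixed function of each man's answers, so if the arms do not differ, its changes have the same distribution in both and the false-positive rate is not inflated. A reader might take p = 0.037 above as a spurious finding under no difference. It is not, because in that example the arms improve in different dimensions. What it shows is that the direction and significance of such a difference are set by digit order.

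**Conclusion.** The point holds for the EQ-5D-3L alone. Taken as written, the sign, ordering and median of the EQ-5D-3L change depend on the order in which the dimensions are written, so the between-arm comparisons at 3, 12 and 24 months cannot be interpreted. The harm is to interpretation. It is not a bias towards either technique or a loss of error control.

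The conclusion rests on a literal reading of the outcome definition together with the analysis rule. It would fall away if a document not shown already names the quantity to be analysed, but the protocol text would still need to be brought into line with it. The EQ-VAS comparison, the primary end-point, the sample size and the interim stop criteria are untouched. This is a correction that should be made to one secondary measure, and it is no threat to the trial's main conclusion.

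**What to change.** Before analysis, state which EQ-5D-3L quantity will be analysed. Either option would do:

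- Convert each profile to an index with one value set, named in advance and used for all centres. Apply the existing change-score and Mann-Whitney rule to that index.
- Classify each man at each visit, against his own baseline, as better (at least one dimension improved, none worse), worse (the reverse), mixed or unchanged. Compare the arms with a categorical test in place of the Mann-Whitney test.

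In both cases, report the five dimensions descriptively by arm and visit. The choice should be made before the data are examined, since the protocol decided against blinding the data analysts.

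The cost is a sentence in the protocol or analysis plan and, for the index, a lookup table. The individual answers are already collected, so no new data are needed. The small downside of the index is that one value set has to be chosen for all centres. Adjustment for baseline is a separate question and is not needed to resolve this point.
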